### 7.3.4 Clinical Laboratory and Other Assessments

A change in the value of a study assessment can represent an AE if the change is a clinically significant worsening from baseline. This includes abnormal assessments where there is a shift of a parameter from a normal value to an abnormal value, or a significant worsening of an already abnormal value. Clinical significance is defined as an abnormal study assessment that leads to a

diagnosis or results in patient intervention such as further monitoring (excluding confirmatory repeat testing) or medical treatment.

*Note: Medications allowed and used as part of SSC to acutely relieve symptoms of COVID-19 (see [Section 6.6](#)) will be captured in the Healthcare Utilization assessment.*

If, at the end of the SP Intake Period, there are abnormal study assessments which were not present pre-treatment, the value observed closest to the start of study treatment should be used as baseline. The PI or designee should decide, based on the above criteria and the clinical condition of a patient, whether a worsening of an abnormal study assessment is clinically significant and therefore represents an AE.

### **7.3.5 Pregnancy**

All pregnancies are to be reported from the time informed consent is signed to the end of follow-up.

Any report of pregnancy for any female study patient must be reported within 24 hours to the Sponsor. Pregnant female patients must be withdrawn from the study.

Every effort should be made to gather information regarding the pregnancy outcome and condition of the infant. It is the responsibility of the PI to obtain this information within 30 calendar days after the initial notification and approximately 30 calendar days and 1-year post-partum.

Pregnancy complications such as spontaneous abortion/miscarriage or congenital abnormality are considered SAEs and must be reported as such. Note: an elective abortion is not considered an SAE.

In addition to the above, if the PI determines that the pregnancy meets SAE criteria, it must be reported as an SAE. The test date of the first positive urine human chorionic gonadotropin test or ultrasound result will determine the pregnancy onset date.

## **7.4 SAE Procedures**

### **7.4.1 SAE Definition**

A SAE is defined as any untoward medical occurrence (whether considered to be related to KB109 or not) that at any dose fulfills at least one of the following criteria:

1. Results in death
2. Is life-threatening

(*Note*: the term “life-threatening” in the definition of “serious” refers to an event in which the patient was at risk of death at the time of the event; it does not refer to an event which could hypothetically have caused death had it been more severe)

3. Requires inpatient hospitalization or prolongation of existing hospitalization

(*Note*: hospitalizations which are the result of elective or previously scheduled surgery for pre-existing conditions, or which have not worsened after initiation of treatment, should not be classified as SAEs. For example, an admission for a previously scheduled ventral hernia repair would not be classified as an SAE; however, complication[s] resulting from a hospitalization for an elective or previously scheduled surgery that meet[s] serious criteria must be reported as SAE[s]).

4. Results in persistent or significant disability/incapacity

5. Is a congenital anomaly/birth defect

(*Note*: congenital anomaly/birth defect in offspring of patient taking KB109 regardless of time to diagnosis)

6. Is an important medical event

(*Note*: important medical events that may not result in death, be life-threatening, or require hospitalization may be considered an SAE when, based upon appropriate medical judgment, they may jeopardize the patient and may require medical or surgical intervention to prevent one of the outcomes listed in this definition. Examples of such medical events include allergic bronchospasm requiring intensive treatment in an emergency room or at home; blood dyscrasias or convulsions that do not result in inpatient hospitalization; or the development of drug dependency or drug abuse)

## 7.4.2 SAE Reporting Procedures

All SAEs occurring from the time a patient signs informed consent until the end of the follow-up period must be reported to Medpace Clinical Safety within 24 hours of the knowledge of the occurrence.

To report SAEs, the site should complete the SAE form electronically in the electronic data capture (EDC) system for the study. When the form is completed, Medpace Safety personnel will be notified electronically by the EDC system and will retrieve the form.

If the event meets serious criteria and it is not possible to access the EDC system, send an email to Medpace Safety or call the Medpace SAE hotline (contact information listed below), and fax/email the completed back up paper SAE form to Medpace within 24 hours of awareness. When the EDC system becomes available, the SAE information must be entered within 24 hours of the system becoming available.

Safety Contact Information: Medpace Clinical Safety  
Medpace SAE reporting line – USA:

[contact] or [contact]  
e-mail: [[contact]](mailto:[contact])  
[contact], dial 3 or [contact], dial 3

### **7.4.3 SAE Collection Timeframe**

All SAEs (regardless of relationship to KB109) are collected from the time the patient signs the informed consent until the end of follow-up and must be reported to the Sponsor and CRO within 24 hours of the first awareness of the event ([Section 7.4.2](#)).

In addition, any SAE considered “related” to KB109 and discovered by the PI or designee at any interval after the study has completed must be reported to the CRO within 24 hours of the first awareness of the event ([Section 7.4.2](#)).

### **7.4.4 SAE Onset and Resolution Dates**

The onset date of the SAE is defined as the date the event meets serious criteria. The resolution date is the date the event no longer meets serious criteria, the date the symptoms resolve, or the event is considered chronic. In the case of hospitalizations, the hospital admission and discharge dates are considered the onset and resolution dates, respectively.

In addition, any signs or symptoms experienced by the patient after signing the informed consent form or leading up to the onset date of the SAE, or following the resolution date of the SAE, must be recorded as an AE, if appropriate.

### **7.4.5 Fatal Outcome**

Any SAE that results in the patient’s death (i.e., the SAE was noted as the primary cause of death) must have ‘Fatal’ checked as an outcome with the date of death recorded as the resolution date. For all other events ongoing at the time of death that did not contribute to the patient’s death, the outcome should be considered ‘Not Resolved’, without a resolution date recorded.

For any SAE that results in the patient’s death or any ongoing events at the time of death, the action taken with the SP should be recorded as “dose not changed” or “not applicable” (if the patient never received SP).

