### **5.5 Withdrawal of Patients**

Patients have the right to withdraw from the study at any time for any reason, without giving a reason and without penalty or loss of benefits they are entitled to. The investigator also has the right to withdraw patients from the study if this is in the best interest of the patient.

Patients will be discontinued from the study in the event of any of the following:

- Patient independently withdraws consent from the study (e.g., patient declines further participation in the study)
- PI determines that the patient has developed a concurrent illness, condition, or an AE due to which continued participation in the study and/or SP dosing is considered potentially harmful to the patient and withdrawal is in the best interest of the patient
- Patient discontinues from SP dosing (i.e., due to development of an AE), but continues his/her consent to participate in the study for follow-up only (e.g., for continued collection of AE information)
- Patient failure to comply with study requirements (e.g., failure to properly consume the SP or failure to comply with other protocol-specific assessments) resulting in protocol deviations that make the interpretation of the data not feasible
- Patient becomes pregnant

Patient requires hospitalization due to worsening COVID-19

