### 5.5.1 Handling of Discontinuation of SP and Early Terminations

If the PI discontinues a patient from SP due to development of an AE, the patient wishes to withdraw from the study, or the patient is terminated from the study for any other reason every effort should be made to:

- Complete the Early Termination visit assessments, as directed in the SOA ([Table 1](#))
- Monitor the patient for resolution of any existing AEs, and onset of new AEs for 3 weeks (21 days) after the last dose of SP.

The data should be documented on the appropriate eCRF in the electronic database capture (EDC) system.

If, due to extenuating circumstances, the PI and/or study site team are concerned that the patient may not be able to safely complete all the required visits and assessments the PI should contact the Sponsor's Medical Monitor to discuss whether an early termination visit should occur to enable the return of the SP, and the completion of key end of intake assessments/measures, while ensuring the patient's safety.

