## **6.8 Dose Reductions and Holds**

In the event of significant worsening of COVID-19 symptoms, severe or intolerable GI symptoms, or other attributable AEs, the KB109 dose may be down-titrated to a lower dose, or temporarily interrupted, after consultation with the Medical Monitor.

KB109 down-titration occurs by reducing the dose in a step-wise fashion. Specifically, a patient's dose can be reduced after evaluation by the PI or designee, and in consultation with the Sponsor's medical monitor or designee from 72 g/day (36 g BID) to 36 g/day (18 g BID) followed by 18 g/day (9 g BID) until the attributable AE resolves or adequate tolerability is achieved.

During the Intake Period, and at the discretion of the PI and in consultation with the Medical Monitor, patients who have down-titrated their KB109 dose may attempt to increase their dose. This up-titration can only occur at the next up-titration period. Patients can also remain at the down titrated dose, for the remainder of the intake period.

If the patient requires down-titration below 18 g/day (9 g/dose BID), then consultation with the Medical Monitor and PI or designee must occur, and the patient may be withdrawn from the study.

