### 8.4.3 Analysis of Endpoints of Interest

#### Adverse Events (AEs)

The analysis of AEs will be based on the Safety Analysis Set. AEs will be coded using the most recent version of Medical Dictionary for Regulatory Activities (MedDRA).

A TEAE is defined as any AE starts or worsens in severity on or after the first dose of SP is taken for SSC + KB109 group or on or after the randomization for SSC group. Adverse event summary tables will include all TEAEs, SP-related TEAEs, SAEs, TEAEs by severity, and TEAEs leading to product discontinuation. Summaries will be presented by MedDRA system organ class and preferred term using frequency counts and percentages by group and overall.

The analysis of the following endpoints will be based on the Full Analysis Set unless otherwise specified.

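### For patients who took KB109, Section 7.4.5 prescribes a 'dose not changed' record for fatal and open-at-death events even where the product had already been reduced, interrupted or stopped for that event

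*Protocol*

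**What the plan says.** Section 7.4.5 sets a coding rule for deaths. It covers two kinds of record, SAEs that led to the death and events still open when the patient died: "or any ongoing events at the time of death, the action taken with the SP should be recorded as “dose not changed". Read to its end, the instruction is that "the action taken with the SP should be recorded as “dose not changed” or “not applicable” (if the patient never received SP"). These are the only two codes it offers, and the choice between them depends only on whether the patient ever received SP.

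Other sections expect SP to be changed because of an adverse event:

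- Section 5.5.1 starts from the case "If the PI discontinues a patient from SP due to development of an AE".
- Section 6.8 says that, for significant worsening of COVID-19, severe or intolerable gastrointestinal symptoms or other attributable events, "the KB109 dose may be down-titrated to a lower dose, or temporarily interrupted".
- Section 5.5 lists among the reasons for discontinuing a patient from the study: "Patient requires hospitalization due to worsening COVID-19".

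Section 8.4.3 then commits to safety output: "Adverse event summary tables will include all TEAEs, SP-related TEAEs, SAEs, TEAEs by severity, and TEAEs leading to product discontinuation". These are counts and percentages by MedDRA class and term, by group and overall. The protocol does not say which data field defines the last of these tables.

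**The concern.** An action-taken field exists to record what was done with the product because of an event. Under 7.4.5, what was done does not enter the rule. A patient who is taken off KB109 for an event and then dies of it, or dies with it still open, must be recorded as having had no dose change for that event. For a patient with the same event who survives, nothing in the protocol overrides the true entry.

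Safety is the primary objective (Section 3.1.1), and the table of TEAEs leading to product discontinuation is one of the summaries planned for it. If the table draws on this field, the cases lost are fatal ones or ones still open at death. The loss can run in one direction only. Under Section 8.3.1 anyone who consumed any KB109 is placed in the KB109 group for safety, and only someone who has taken the product can stop it. An omission can therefore only make KB109 look better tolerated.

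**Working it through.** The point rests on no figure stated in the protocol, so the main check sets the sections side by side.

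**Step 1: what the rule depends on.** Its inputs are (a) whether the event was fatal or open at death and (b) whether SP was ever received. Its output is *dose not changed* or *not applicable*. The action really taken is not an input.

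| Patient and event | What was done with SP | Code under 7.4.5 | Correct? |
|---|---|---|---|
| Never received SP | Nothing to change | Not applicable | Yes |
| Received SP, no action for the event before death | None | Dose not changed | Yes |
| Received SP, reduced or interrupted for the event | Reduced or interrupted | Dose not changed | No |
| Received SP, stopped for the event | Stopped | Dose not changed | No |

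The third and fourth rows are wrong records. Only the fourth bears on the discontinuation table.

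**Step 2: can the fourth row arise?** Yes. COVID-19 worsens during intake, the patient is hospitalized and discontinued under 5.5, and later dies. The hospitalization is an SAE under 7.4.1, and 7.3.3 does not exempt hospitalizations as expected disease symptoms. The death would be captured, because 5.5.1 asks for 21 days of monitoring after the last dose and 7.1 requires events to be followed to closure even after the patient has left the study.

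**Step 3: which records does it reach?** Not all of them. Section 7.2.1 has a change in severity captured as a new event. Section 7.4.4 dates an SAE from when it meets serious criteria and has earlier signs or symptoms recorded as an AE where appropriate. An SP action may therefore sit on an earlier, closed record that is neither fatal nor open at death, and 7.4.5 leaves that record alone. The rule bites when the SP action belongs to the record that is itself fatal or still open, for example SP stopped at hospitalization with no later change in severity.

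**Step 4: how often?** The protocol gives no expected mortality, so the rates p below are assumptions. With n = 175 to 200 patients in the KB109 group (synopsis, number of patients planned), the chance of at least one death from any cause is 1 − (1 − p)^n:

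| Assumed p | Expected deaths (n × p) | n = 175 | n = 200 |
|---|---|---|---|
| 0.1% | 0.175 to 0.2 | 16.1% | 18.1% |
| 0.5% | 0.875 to 1.0 | 58.4% | 63.3% |
| 1% | 1.75 to 2.0 | 82.8% | 86.6% |

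These are upper bounds for the problem, since an affected death also needs SP to have been stopped for that same record. SP is taken only on Days 1 to 14, while follow-up runs to Day 35. As a further assumption, let 25% to 50% of deaths qualify. At p = 0.5% and n = 200:

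- 25%: 1 − (1 − 0.00125)^200 = about 22%
- 50%: 1 − (1 − 0.0025)^200 = about 39%

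Expected affected patients over the whole range run from 175 × 0.001 × 0.25 = 0.04 to 200 × 0.01 × 0.50 = 1.0.

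**Step 5: weight of one case.** 1/200 = 0.50 and 1/175 = 0.57 percentage points of the KB109 discontinuation rate.

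**The case against.** The strongest reply is that this is a recording convention with little reach.

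- **The table's source is not stated.** Section 8.4.3 names the table but not its field, and the detail is left to an SAP that is not at hand. Section 5.5.1 asks for discontinuation data on the appropriate eCRF, 8.4.1 tabulates reasons for discontinuation, and SP dosing logs are kept. The event could be counted from one of these. This stands, and the effect on the table is therefore conditional. It does not cure the false entry, which would then contradict the other source. Nor are these clean substitutes: the disposition summary works per patient, and the logs as described hold date, time and amount, not the event that prompted a change.
- **Records are split** (step 3 above). This stands and narrows the problem.
- **Little else depends on the field.** The primary endpoint, patients with SP-related TEAEs (3.2.1), does not use it. A treatment-emergent fatal event still appears in the all-TEAE, SAE and severity summaries, with a fatal outcome recorded. This stands.
- **Mortality should be low.** Section 5.2 excludes patients judged likely to need hospitalization, on oxygen, or short of breath at rest. This makes the upper assumed rates less plausible.

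A reader might infer that every death-related event is coded *dose not changed*, that none can reach the discontinuation table, or that the most serious discontinuations are removed by construction. The text does not support this. Patients who never received SP get the other code, the table's source is open, and actions held on earlier closed records are not overwritten.

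**Conclusion.** The defect holds in a limited form. For a patient who received SP, 7.4.5 requires an untrue action-taken entry whenever SP had been reduced, interrupted or stopped for the same record that is fatal or open at death. That conflicts with 5.5.1 and 6.8. It follows from the wording alone and needs no assumption about rates.

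The effect on the table of TEAEs leading to product discontinuation rests on one assumption, that the table uses this field. If so, the omission falls only among patients who took KB109 and favours the product. The likely size is none or one patient, at 0.5 to 0.6 percentage points each. The any-death probabilities of 16% to 87% rest on assumed mortality and must not be read as the chance of an affected case.

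The correction is worth making because the records at risk are among the most serious in the trial and the remedy is cheap. The trial's primary result is not in doubt on this account.

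**What to change.** Reconcile 7.4.5 with 5.5.1, 6.8 and 8.4.3 by adding an exception to the coding sentence, for example: *unless another SP action (reduced, interrupted, discontinued) was taken for the event before death, in which case that action is recorded*. Keep the two present codes as the default otherwise, so that death alone is still not coded as withdrawal of the product. Where the discontinuation table is specified, name its source field so that fatal events are eligible.

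The cost is one clause in the protocol and the matching line in the eCRF completion guideline. It changes recording only and leaves every dosing and stopping rule as it is. The downside is that the reported KB109 discontinuation rate may come out slightly less favourable.

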### **7.4.6 Reporting to health authorities, independent ethics committee and investigators**

The PI must comply with any applicable site-specific requirements related to the reporting of SAEs (and in particular deaths) involving his/her patients to the Independent Ethics Committee

(IRB) that approved the trial. In accordance with ICH-GCP guidelines, the Sponsor will inform the PI of “findings that could adversely affect the safety of patients, impact the conduct of the trial, or alter the IRB’s approval/favorable opinion to continue the trial.” In line with respective regulations, the Sponsor will inform the PI of AEs that are both serious and unexpected and are considered to be related to the administered product (“suspected unexpected serious adverse reactions”). The Sponsor will send appropriate safety notifications to relevant health authorities if required in accordance with applicable laws and regulations.

The PI should place copies of safety reports in the Investigator Site File (ISF). National regulations regarding safety report notifications to the PI will be taken into account. When specifically required by regulations and guidelines, the Sponsor will provide appropriate safety reports directly to the concerned IRB and will maintain records of these notifications. When direct reporting by the Sponsor is not clearly defined by national or site-specific regulations, the PI will be responsible for promptly notifying the concerned IRB of any safety reports provided by the Sponsor and of filing copies of all related correspondence in the ISF.

## 8 STATISTICAL CONSIDERATIONS

This section outlines the statistical analysis strategy and procedures for the study. The details of the statistical methods will be provided in a separate technical document or in the Statistical Analysis Plan (SAP).

### 8.1 Sample Size Justification

The study will enroll approximately 350 to 400 patients. The enrollment target is based on practical reasons. Assuming a 15% attrition rate, this will provide approximately 296 to 340 evaluable patients (148 to 170 per group).

The precision of the point estimate in terms of half-width of the 95% confidence interval (CI) of the AE rate is summarized for a range of evaluable number of patients and assumptions on the SP-related TEAE rates. A larger (or smaller) number of patients will provide narrower (or wider) CIs, and the CI would be narrower for rarer events with lower event rates.

**Table 4 Half-width of the 95% CI for SP-related TEAE Rate**

| Evaluable Sample Size
(N/Group) | SP-Related TEAE
Rate | 95% CI  | Half-Width of the
95% CI |
|--------------------------------------------|---------------------------------|----------------|-------------------------------------|
| 148                                        | 10%                             | [5.8%, 16.2%]  | 5.2%                                |
|                                            | 20%                             | [14.1%, 27.7%] | 6.8%                                |
|                                            | 40%                             | [31.9%, 48.2%] | 8.2%                                |
|                                            | 60%                             | [51.8%, 68.1%] | 8.2%                                |
| 170                                        | 10%                             | [5.9%, 15.5%]  | 4.8%                                |

|  |     |                |      |
|--|-----|----------------|------|
|  | 20% | [14.3%, 26.8%] | 6.3% |
|  | 40% | [32.6%, 47.8%] | 7.6% |
|  | 60% | [52.2%, 67.4%] | 7.6% |

